**Fig 2 pone.0319020.g002:**
[figure not shown]
Cynnau|Ignite streams and modules, mapped against relevant dimensions of the UKRI Research Culture Framework.

The programme’s tailored training sessions are hypothesized to help learners promote positive values and attitudes towards PRC, develop a relevant skill set (research career development, leadership) leading to higher perceived efficacy in enacting PRC, and aid in the creation of a community of practice that normalises PRC. In turn, according to the Theory of Planned Behaviour these elements should lead to the creation of strong intentions to practice, and advocate for, PRC and its subsequent behavioural enaction, which is supported by the Action Learning stream of the programme. Learners’ enaction of PRC practices is also expected to lead to improvements in stakeholders’ perceptions of, and in organisational indicators of, PRC at Cardiff University.

Cynnau|Ignite will be run as an interactive programme and all members of the delivery team have experience with participant engagement and a background in designing and implementing training programs for leadership, research skills and/or culture. Except for the Influencing Change module, all content was designed by a network of internal Cardiff University specialists aided by contributors such as specialists or Heads of School, who have specific knowledge and skills pertaining to the session they have been asked to lead. However, Influencing Change will be delivered by an external provider, 64 Million Artists, due to their expertise in creative leadership and helping academics to raise their research ambitions and shape thriving university environments. This provider was able to take a part of their existing “Leading Researchers” programme and create bespoke content to meet the requirements of Cynnau|Ignite’s Influencing Change learning outcomes. Discussions between both parties demonstrated similarities in leadership ethos and partnering expectations, for example, enthusiasm about creativity, belonging, and meaningful connections. Compared to other external providers, 64 Million Artists were able to provide additional strengths mapping opportunities, as well as make all session dates within the budget expected.

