**Fig 3 pone.0319020.g003:**
[figure not shown]
Cynnau|Ignite Theory of Change describing inputs, activities and anticipated short-term outcomes. Potential Moderators and Unintended Consequences are outlined in red.

The effectiveness quantitative evaluation (displayed alongside Cynnau|Ignite’s implementation plan in Fig 1) is a prospective evaluation with three assessment moments: within two weeks of the start of the programme (baseline – T1), and two weeks following the final session (short-term follow up – T2), then six months after the end of the programme (mid-term follow up – T3). Fig 4 presents the Participant Flowchart. All cohorts will complete the baseline and short-term follow up, with an additional mid-term follow up for the R-only cohort (as course timetabling allows). A control group of university staff who did not take part in Cynnau|Ignite will fill in the baseline and short-term follow up with a 6-month gap in between, which equals the shorter period of Cynnau|Ignite implementation across the three groups (i.e., for the PST/S group) and is therefore comparable with the baseline and short-term follow up assessments for the cohorts.

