### Outcomes

The study outcomes are presented in Table 1, organized per the study’s research questions and Bowen’s framework [16] which evaluates different areas of intervention implementation that are directly relevant to our research aims.

**Table 1 pone.0319020.t001:** Cynnau|Ignite’s evaluation outcomes (organised by research question), methods and informants for evidence gathering.

	Dimension evaluated*	Outcomes	Informants		
			Learners	Stakeholders	Delivery Team
**Research Q1**	**Acceptability** How well is Cynnau|Ignite received?	Expected (positive and negative) outcomes of attending themes and overall participation in Cynnau|Ignite, for learners and their school/unit	PE	PE	PE
		Perceived (positive and negative) outcomes (and cost-benefit) of attending themes and overall participation in Ignite, for learners and their school/unit	PE	PE	PE
	**Integration** How well can Cynnau|Ignite be integrated into Cardiff University?	Perceived disruption(s) caused by Cynnau|Ignite	PE	PE	PE
	**Effectiveness** To what extent is Cynnau|Ignite successful in achieving its goals?	Perceptions about what in Ignite contributed to outcomes perceived and how	PE	PE	PE
		Perception about for who and under what circumstances does Ignite contribute (or not) to outcomes	PE	PE	PE
	**Impact** The short- and longer-term effects or influence of Cynnau|Ignite	Perceptions about long-term impact(s) of staff attending Ignite (e.g., career development) at personal, school, and Institutional level	PE	PE	PE
		Perceived impact from and plans to continue/extend Action Learning projects (e.g., other contexts, further developments, networks, etc.)	PE	PE	PE
**Research Q2**	**Demand** To what extent is Cynnau|Ignite likely to be used?	Number of brochures requested	DM		
		Number of EoI submitted	DM		
		Final number of participants & per/school	DM		
		Background and professional profile of applicants	PE		
		Perceptions of demand	PE	PE	PE
		Attendance rate	DM		
		Attendance rate for optional Action Learning module (R)	DM		
		Contributors and learners’ engagement during sessions	OBS		
	**Acceptability** How well Cynnau|Ignite is received? Is it suitable and appropriate to meet the needs of participants, stakeholders and the delivery team?	General views of and feedback about Cynnau|Ignite	PE	PE	
		Perceptions of most and least useful elements or sessions of Ignite	PE		PE

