		For each Stream: multiple Likert-type questions assessing acceptability of content and delivery, plus one open-ended question for additional feedback	SE		
		Observation of and feedback/comments from participants re acceptability during sessions	OBS		
**Research Q3**	**Implementation** To what extent can Cynnau|Ignite be delivered as planned?	Perceptions of barriers and facilitators of programme implementation			PE
		Description of changes to planned implementation and rational			PE
		Description of changes to planned implementation and rational			DM
		Description of changes happening during sessions and rational	OBS		
	**Practicality** Can Cynnau|Ignite be carried out as planned with the resources available?	Perceptions of barriers and facilitators of attendance	PE	PE	PE
		Perceptions of barriers and facilitators of implementing Action Learning projects	PE	PE	PE
		Perceptions of barriers and facilitators of general enactment of Cynnau|Ignite learning, skills, and values	PE	PE	PE
		Observation of and feedback/comments from participants re practicality during sessions	OBS		
	**Adaptation** How well can we expect Cynnau|Ignite to perform at other HEIs or staff career development levels?	Perceived challenges of implementing Ignite at other HEIs or staff career development levels	PE		PE
		Perceived changes needed to implement Ignite at other HEIs or staff career development levels	PE	PE	PE
	**Integration** How well can Cynnau|Ignite be integrated into Cardiff University?	Perceived organizational fit of Cynnau|Ignite (resources, culture, practicalities…)	PE	PE	PE
		Perceptions of sustainability of implementing Cynnau|Ignite	PE	PE	PE
		Observation of and feedback/comments from participants re fit of Ignite with organizational environment/procedures during sessions	OBS		
**Research Q4**	**Effectiveness** To what extent is Cynnau|Ignite successful in achieving its goals?	Analyses on TPB outcomes (intentions, attitudes, norms, perceived behaviour control) measured at T1 and T2.	QE		
		Differences in TPB outcomes (intentions, attitudes, norms, perceived behaviour control) for R-only learners, measured at T2 and T3	QE		
	**Impact** The short- and longer-term effects or influence of Cynnau|Ignite	Differences in perceptions of PRC at Cardiff University, as measured in the Research Culture Survey, between all Ignite learners and a matched group of CU staff who did not participate in Ignite, and between learners and control group.	QE		

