### Participants

The intervention group will consist of all learners, comprised of four cohorts (two T&R cohorts, one R and one PST/S cohort) with 32 learners in each. All those accepted into Cynnau|Ignite will be eligible to take part in the study and will integrate the intervention trainee groups. Selection criteria for Cynnau|Ignite will be those employed at Cardiff University at grade six, seven or eight as Teaching and Research, and Research-only staff, along with Professional Service staff, or Technicians at grades 5 to 8, in any discipline. Applicants will be expected to demonstrate that they have an interest in PRC and are available to attend all sessions, with allowances made for those who are unable to attend a single session. These criteria mirror common practice for similar training programmes at Cardiff University and will be likely to remain unchanged, unless if demand will need to be addressed in future Cynnau|Ignite iterations. We expect high participation and low attrition in the intervention group. No concealment or blinding will be used in this research. All learners will be allocated to either the Teaching and Research, Research-Only, or Professional Services, Technicians and Specialists version depending on their career path.

Inclusion criteria for the control group will be being a Cardiff University employee at grade six, seven, or eight who is not enrolled in the programme. Based on moderate attrition rates between 20–50% [17,18] observed in repeated measures surveys and organizational research, we intend to recruit a total of 96 staff members for this group, with a maximum of 32 participants each from T&R, R and PST/S roles. A power analysis conducted using GPower [19] indicates that this will provide enough power to detect small to moderate effect sizes (repeated measures ANOVA, p = .90, f =  0.15, α = .05) in differences between the learner and control groups in changes in intentions from baseline (T1) to follow up (T2) and in differences between the R and control groups in changes in intentions from baseline (T1) to follow ups (T2 & T3).

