Effectiveness and impact (Research Question 4) will be reported for all learners, but the analytical strategy will depend on the final sample achieved. Cardiff University has a total of 26 academic schools, all of which are eligible for Cynnau|Ignite. To account for non-independence of data we will use multi-level modelling [30] with learners (level 1) nested within schools (level 2), but only if the recommended 20 schools/units are achieved [31]. If this is not possible, we will use two-way Mixed ANOVA. Analysis will investigate how Cynnau|Ignite affects self-reported intentions and actual PRC behaviours (primary outcomes), attitudes, norms and PBC (secondary outcomes), with Group (Cynnau|Ignite, Control) as the between-subject variable and Time (T1, T2) as the within-subject factor. Similar analysis will be used to compare each Cynnau|Ignite group (T&R, R, PST/S) with the control group and to investigate changes in the study outcomes across a 6-month period following Cynnau|Ignite, the latter with Time (T2, T3) as the within subject factor for the R-only cohort. Statistical significance will be indicated if *p* < 0.05 and effect sizes will be reported for all analysis. Finally, we will quantitatively analyse the organisational impact of Cynnau|Ignite by investigating learner and control group differences with multilevel modelling, or Mixed ANOVA if the necessary units are not reached, in perceptions of PRC at Cardiff University. Descriptive and inferential statistics will be used to map the impact of Cynnau|Ignite on impact indicators, such as the implementation of Action Learning projects related to research culture, and learners’ uptake of mandatory staff training compared to those who did not participate in Cynnau|Ignite.

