Third, this study will provide comprehensive data about the impact of Cynnau|Ignite at organizational level, therefore directly reliably addressing the fundamental question of if, which, and how systemic change in RC can be achieved. Unfortunately, the time-limited nature of this funded project does not allow us to examine the sustainability of this change beyond 6-months (if any), nor does it allow us to capture the full extent of changes which may only manifest in the long-term (ripple effects), as is often the case in complex organisations like Cardiff University. However, evaluation findings will increase HEIs and funders’ understanding of how best to invest in PRC (especially in a context of reduced funding), by contributing insights into what are the most effective contributions of the programme, what are common barriers to and how do these obstruct change in PRC, how to scale up Cynnau|Ignite or similar initiatives to maximize organizational impact, and how to measure this in the longer term.

A fourth contribution of this project is advancing meta-research in higher education, by testing the application of the TPB [9] in this context and its integration with the UKRI research culture framework that forms the basis of our evaluation. While the UKRI framework constitutes significant conceptual advance in the definition of PRC [4], our TPB-based assessment constitutes a proposal for operationalising this holistic concept in a way that can be used to measure change.

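### The six-month analysis is fixed as T2 versus T3 in the R-only cohort without T1, and the R-versus-control comparison at T3 that the power statement covers cannot be run

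*Protocol article*

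**What the plan says.** Three parts of the protocol article describe the six-month question, and a fourth decides what data exist for it.

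- **Analytical methods.** Change over the six months after the programme is analysed "the latter with Time (T2, T3) as the within subject factor for the R-only cohort". The main model and the comparisons of each learner group with control use T1 and T2.
- **Table 1, Research Q4.** The outcome is given as "Differences in TPB outcomes (intentions, attitudes, norms, perceived behaviour control) for R-only learners, measured at T2 and T3".
- **Participants (power statement).** Power of 0.90 at f = 0.15 and alpha 0.05 is claimed for learners versus control from T1 to T2, and also "in differences between the R and control groups in changes in intentions from baseline (T1) to follow ups (T2 & T3".
- **Study design.** Every cohort completes T1 and T2, "with an additional mid-term follow up for the R-only cohort (as course timetabling allows". The control group completes T1 and T2 only, six months apart.

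The Discussion says the funding period "does not allow us to examine the sustainability of this change beyond 6-months (if any", which implies that durability up to six months is something the study will speak to.

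**The concern.** The natural durability question is whether scores six months after the programme are still above where they started. The specified contrast asks something narrower: whether scores moved after the programme ended. A flat T2-T3 result fits a gain that was kept, and it fits equally well no gain at all. A fall from T2 to T3 cannot be graded as partial or complete loss without the baseline. The baseline is measured in the same people, so the information is available and unused.

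The power statement describes a baseline-anchored, controlled comparison at T3 that the analysis section does not contain and the data cannot supply. A reader of Participants would expect a powered, controlled six-month result. What is planned is an uncontrolled contrast in one cohort of 32, for which no power is stated. This is the protocol's only planned survey comparison of lasting change in the theory-based outcomes.

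**Working it through.** **Inputs from the protocol.** R cohort 32; control target 96; f = 0.15; alpha 0.05; power 0.90; attrition of 20-50% in comparable surveys (low attrition is expected in learners). **Assumed:** correlation r between assessments, which is not stated: 0.5, range 0.3 to 0.7. The smaller sample sizes are sensitivity values: 32 × 0.8 ≈ 26 and 32 × 0.5 = 16.

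**1. The plan's own figure.** For a group-by-time interaction with m assessments and total N, the noncentrality is λ = f² × N × m / (1 − r).
- Two groups, three times, N = 96: λ = 0.0225 × 96 × 3 / 0.5 = 12.96, power 0.902.
- Two groups, two times: 0.90 needs N = 119.

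So 0.90 is reproduced if 96 is the total sample in a two-group, three-time design. In the protocol 96 is the control group alone, and that group has two times.

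**2. What can be run for R versus control.** Only T1-T2. With equal groups, f = 0.15 on the interaction is a difference in change of 4 × 0.15 = 0.6 SD. The SD of change is √(2(1 − r)) = 1 at r = 0.5.
- SE = √(1/32 + 1/96) = 0.204, and 0.6 / 0.204 = 2.94, so power is about 0.84 (0.70 at r = 0.3, 0.97 at r = 0.7).
- With 48 controls retained, about 0.75 at r = 0.5.

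At T3 the control sample is zero.

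**3. The specified T2-T3 test.** For a paired test, the noncentrality is d × √n / √(2(1 − r)). If a gain d is fully lost, the T2-T3 fall is d. At n = 32 and r = 0.5 this is 0.3 × √32 = 1.70 or 0.6 × √32 = 3.39.

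| Gain fully lost | n = 32 | n = 26 | n = 16 |
|---|---|---|---|
| 0.3 SD (f = 0.15 on a two-level time factor) | 0.38 | 0.31 | 0.20 |
| 0.6 SD (f = 0.15 read as the interaction) | 0.91 | 0.84 | 0.61 |

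Over r = 0.3 to 0.7 at n = 32, the ranges are 0.29 to 0.57 for 0.3 SD and 0.79 to 0.99 for 0.6 SD. A simulation of 20,000 runs agrees: full loss of 0.3 SD is non-significant in 62% of runs at n = 32 and 69% at n = 26; for 0.6 SD at n = 32 it is about 9%.

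**4. What adding T1 does and does not do.** An overall three-time test at f = 0.15 and n = 32 has λ = 0.0225 × 32 × 3 / 0.5 = 4.32 and power 0.43, little better than 0.38. The benefit is in the question answered. Under full loss the true T3 − T1 is zero, so a two-sided 5% test wrongly declares a lasting gain about 2.5% of the time. By symmetry, T3 − T1 has the same 38% power to detect a fully kept 0.3 SD gain.

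**5. Precision of T3 − T1.** The 95% CI half-width is about 0.36 SD at n = 32, 0.40 at n = 26 and 0.52 at n = 16. An observed T3 − T1 of 0.30 SD at n = 32 would carry an interval of about −0.06 to 0.66.

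**The case against.** The strongest reply is that a fully lost gain is exactly a fall from T2 to T3, so the planned contrast already measures it. That is right. A reader might infer that leaving out T1 lets a complete loss pass as no change. It does not: a loss is missed through low power in at most 32 people, and adding T1 barely alters that.

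Second, the same paragraph of Analytical methods compares the R group with control over T1-T2, so the plan does ask whether there was a gain. This also stands. But two separate tests do not give an estimate of T3 against T1, and they do not grade a later fall.

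Third, nothing in the protocol says that a non-significant result will be taken as maintenance. Effect sizes are promised for all analyses, and the Discussion sentence is worded as a limitation. The misreading is a risk to guard against, not a stated rule.

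Fourth, a reader might infer that the six-month result will be presented as that of the whole programme, because Table 1 lists "Attendance rate for optional Action Learning module (R" among the demand outcomes. The protocol does not support this: it labels the T3 analysis R-only throughout, and the Discussion already says that the R version is truncated and that benefits may differ between groups. Whether the optional module is the whole Action Learning stream depends on figures not shown here.

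What no objection removes is the disagreement between sections: Participants names changes from T1 to T2 and T3 against control, Analytical methods and Table 1 use T2 and T3 within R, and Study design gives controls no T3.

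**Conclusion.** The point holds as an internal inconsistency plus an avoidable gap in a specified analysis. The six-month contrast leaves out baseline data held on the same learners, so alone it cannot show whether scores remain above baseline. The power claimed for R versus control at T3 attaches to a comparison with no control data. With no control at T3, change after T2 also cannot be separated from wider change at the university or in the sector.

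The size of the problem depends on the effect. At n = 32 and r = 0.5, a non-significant T2-T3 result would occur about 62% of the time after complete loss of 0.3 SD, but only about 9% of the time after complete loss of 0.6 SD. Both the correlation and the reading of f are assumptions. The finding does not show that the plan would systematically misreport a lost gain, or that the authors intend to equate non-significance with maintenance. It is a moderate point that should be corrected because the remedy is nearly free.

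**What to change.** - **Analytical methods and Table 1:** fit the R-only model with Time = T1, T2, T3. Make T3 minus T1 with its 95% CI the durability estimate, and report T3 minus T2 with its 95% CI. State that a non-significant T3-T2 difference will not be read as maintenance.
- **Reporting:** label the six-month result as uncontrolled and as applying to the R version only.
- **Participants:** remove the claim of power for R versus control at T3. State which N, number of assessments and correlation the 0.90 refers to, and limit the R-versus-control claim to T1-T2.

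The cost is wording and one re-specified model on data already planned. The downside is that T3 minus T1 remains uncontrolled and imprecise (half-width about 0.36 SD at n = 32, wider with attrition), so it may well be inconclusive for a small gain.

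Two further steps may look attractive but are not recommended as cheap repairs. Splitting the R cohort by Action Learning attendance would divide at most 32 people on a self-selected variable. Extending T3 to PST/S learners depends on start dates the protocol does not give. If that cohort started near the 8 January 2025 close of recruitment, a two-week window, a six-month programme and six months of follow-up would end about 22 January 2026, roughly 10 days before the stated project end of 1 February 2026.

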Stakeholders will be able to describe, and in many cases may have helped define, the programme’s purpose, and how it seeks to create change. Expectations of the overall cost/benefit will differ based on perspective (e.g., Heads of School and line managers may perceive greater disruption resulting from Cynnau|Ignite, compared to the delivery team).All stakeholders will value the programme, while understanding that the learners’ ability to translate intentions to engage with PRC into actual behaviours will depend on barriers and facilitators they experienced throughout.Implementing Cynnau|Ignite at Cardiff University will be feasible and practical due to its bespoke nature and close alignment with university values. We expect that immersing learners in an environment which directly fosters Cardiff University’s PRC aims, with support from senior management, will facilitate adoption of the programme. Additionally, the iterative, adaptable and bespoke nature of this programme may increase the feasibility of its wider adoption, and potential implementation in other institutions. However, we predict it’s high-resource design will make implementation and adoption vulnerable to common barriers such as lack of time, financial and human resources.Cynnau|Ignite will be acceptable and effective in increasing learners’ intentions of PRC practices at Cardiff University, compared to a control group of staff who did not participate in Cynnau|Ignite. We expect this difference to be evident across multiple dimensions of the UKRI PRC framework targeted (specifically research integrity, open approach to research, communicating research, ensuring an inclusive work environment, building collegiality, and realising impact [4]). Finally, we expect learners’ enaction of PRC practices will have a ripple effect at organisational level, improving perceptions of and indicators of PRC at Cardiff University.

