Structured observations will also be used to investigate learners’ engagement with, and reactions to, the programme content. A total of 12 half-day Cynnau|Ignite sessions, split between am and pm sessions, were randomly selected for observation (approximately three per cohort). Using a modified version of Lane and Harris’ Tool for Measuring Student Behavioural Engagement [24] which we tailored to ensure the tool sufficiently captured the behaviour of university staff in an active-learning programme, we will note the number of learners exhibiting specific behaviours such as reading, writing, and making eye contact with the facilitator, at ten-minute intervals throughout observation sessions. This data will be noted anonymously, and at group level, along with narrative annotations where necessary for context.

Process evaluation data will be collected via semi-structured interviews and based on realist principles [25,26]. We aim to collect participants’ views about the outputs (positive, negative) triggered by Cynnau|Ignite and how (theory of change), for whom, and under which circumstances these are triggered [27,28]. Finally, impact evaluation data will be collected via desk review and the above-mentioned interviews, and overall perceptions of PRC at Cardiff University will be measured in the biennial Research Culture Survey. (https://www.cardiff.ac.uk/documents/2741029-research-culture-survey-report-2023-executive-summary), and compared between the intervention and control groups.

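### Organisational impact is tested as a learner-versus-control difference within one university, which can neither show nor exclude the hypothesised ripple effect

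*Protocol article*

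**What the plan says.** The last hypothesis under Objectives is that learners' enaction of positive research culture (PRC) "will have a ripple effect at organisational level, improving perceptions of and indicators of PRC at Cardiff University". The programme description likewise expects stakeholders' perceptions to improve. Objectives counts heads of school, line managers and senior management among the stakeholders, so the expected benefit extends to people who did not attend.

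Under Materials, "overall perceptions of PRC at Cardiff University will be measured in the biennial Research Culture Survey", and these are to be "compared between the intervention and control groups". In Table 1 (Outcomes), the impact row for this survey sets out a comparison "between all Ignite learners and a matched group of CU staff who did not participate in Ignite", and a second one between learners and the control group. Analytical methods gives the test: "we will quantitatively analyse the organisational impact of Cynnau|Ignite by investigating learner and control group differences", by multilevel model, or by Mixed ANOVA if too few schools or units are reached.

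The control criterion under Participants is "being a Cardiff University employee at grade six, seven, or eight who is not enrolled in the programme". Recruitment approaches staff who showed interest in the programme first. All 26 academic schools are eligible for the programme.

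The Discussion describes the study as "directly reliably addressing the fundamental question of if, which, and how systemic change in RC can be achieved".

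**The concern.** The hypothesis is about a change in the environment that learners and controls share. The planned contrast measures what learners have and controls do not. Both groups rate the same institution, and whatever spreads to controls is subtracted from the estimate. The quantity estimated is therefore not the quantity hypothesised.

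The Discussion intends the findings to guide investment in research culture at Cardiff and elsewhere. A null could be read as no organisational effect when the benefit had spread. A positive difference could be read as systemic change when it shows only that attendees see the university differently from non-attendees.

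**Working it through.** **1. The protocol's own figure.** Participants gives 96 controls, power .90, f = 0.15 and α = .05 for a repeated measures ANOVA on changes in intentions. The correlation between repeated measures, ρ, is not stated; 0.5 is assumed. For the group-by-time interaction, λ = f²·N·m/(1 − ρ), with g groups, m times and total sample N.
- g = 2, m = 3: λ = 0.0225 × 96 × 3 / 0.5 = 12.96, power 0.902. The figure of 96 reproduces as a total N.
- g = 2, m = 2: total N of 119 is needed (120 with equal groups, power 0.903). The planned 128 + 96 = 224 gives 0.994.
- For ρ from 0.3 to 0.7, required N runs from 133 to 58 (m = 3) and from 166 to 73 (m = 2).

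This calculation concerns intentions. It does not cover the organisational outcome, and it does not model spillover.

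**2. What the contrast estimates.** Let L be the programme-induced change in learners and K the programme-induced change in controls. The contrast is C = L − K. The ripple to non-participants is in K. One observed difference cannot separate the two quantities.

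- *Shared fraction.* Controls receive K = s·L, with 0 ≤ s ≤ 1. Then C = (1 − s)·L.
- *Equal additive ripple.* Learners gain D + r and controls gain r. Then C = (D + r) − r = D, whatever r is. With D = 0.30, C is 0.30 at r = 0, 0.3 and 0.6. With D = 0, C is 0 and the test rejects at its nominal 0.05.

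**3. Illustrative size under the shared fraction.** Assumptions: the learner gain equals the effect implied by f = 0.15 in a 2 × 2 interaction, d = 4f = 0.60 SD; ρ = 0.5; all 128 learners respond. Controls number 77 (96 × 0.80) or 48 (96 × 0.50), the ends of the 20–50% attrition range under Participants. The standard error of the difference in change is √[2(1 − ρ)(1/n₁ + 1/n₂)]. For 128 v 77 this is √(1/128 + 1/77) = 0.144.

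| s (assumed) | Contrast (SD) | Power, 128 v 77 | Power, 128 v 48 |
|---|---|---|---|
| 0 | 0.60 | 0.985 | 0.941 |
| 0.25 | 0.45 | 0.874 | 0.753 |
| 0.50 | 0.30 | 0.544 | 0.422 |
| 0.75 | 0.15 | 0.179 | 0.143 |
| 0.90 | 0.06 | 0.070 | 0.064 |
| 1 | 0 | 0.050 | 0.050 |

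**4. Reading the result.** Under the first model, the difference is largest when nothing has spread. Under the second, it carries no information about spread. A null fits no effect, complete spread, or a ripple with no learner-only benefit.

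**The case against.** **The impact evaluation does not rest on this contrast alone.** Table 1 also lists interviews on impact at personal, school and institutional level, Action Learning project counts and narratives, and the institution's funding decision. The Discussion relies on triangulation across methods and informants. This stands, so it would be wrong to infer that the study has no evidence on organisational impact. But that evidence is descriptive or qualitative, and the other between-group indicator, uptake of mandatory training, again compares learners with non-participants.

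**The protocol already qualifies its claim.** The Discussion concedes that long-term ripple effects may be missed and that an unmatched control group makes wider sector changes hard to separate. Neither concession says that controls are themselves exposed to the ripple.

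**A Mixed ANOVA would contain the ripple in its Time effect.** So it would, mixed with secular change, and Analytical methods does not name that effect as the test.

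A reader might also infer more than the documents support:
- *That the test runs in the opposite direction to the hypothesis.* For s between 0 and 1, (1 − s)·L never changes sign.
- *That a successful ripple must shrink the contrast.* This needs controls to converge on learners; an equal additive ripple leaves it unchanged.
- *That a real systemic effect yields a null.* In expectation that needs s = 1 or no learner-only effect. At s = 0.25 the illustrative power is still 0.87 with 77 controls. The Discussion's expectation that ripple effects may take a long time also argues against complete spread over the six-month control interval.
- *That controls work in the same schools as learners.* All schools are eligible, but nothing states where controls will work.

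**Conclusion.** The concern holds as a mismatch between hypothesis and estimand; it is not an arithmetic error. The contrast is either attenuated by the ripple, to (1 − s) of the learners' gain, or blind to it. It cannot serve as the test of organisational impact and does not support the Discussion's wording on systemic change.

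The structural conclusion needs only that controls belong to the university whose culture is expected to change, which the protocol states. The sizes in the table rest on assumed values of s, ρ and d and are illustrations only.

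The point is confined to the organisational outcome. The primary outcomes (intentions and behaviours) and the power statement do not depend on it.

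**What to change.** **Wording changes, needing no new data:**
1. In Table 1, Materials and Analytical methods, call the learner-versus-control difference in perceptions a participant-level perception outcome, and stop presenting it as the test of organisational impact.
2. In the limitations paragraph of the Discussion, state that controls are exposed to any ripple, so a null does not exclude one and a positive difference does not demonstrate one.
3. In the Discussion, limit the claim about systemic change to what the descriptive and qualitative evidence can support.

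**An analysis closer to the hypothesis, if feasible:** report the change in Research Culture Survey scores among non-learners between the 2023 wave and the next one. If the survey records school and learners can be identified, relate that change to learners per school as an exploratory analysis; Table 1 already monitors participant numbers by school.

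**Cost and limits.** The wording costs almost nothing. The added analysis depends on a later survey wave, which the article does not show to be available. It is observational and confounded with the secular change that the Discussion acknowledges. It would also be imprecise: there are at most 26 schools, and 128 / 26 is about 4.9 learners per school, fewer if some professional services learners sit outside schools. It should be reported as supporting evidence and not as a definitive test.
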